### Exploratory analyses

#### Vascular resistance-cortical stiffness relationship in pAKI

The relationship between renal vascular indices in the form of renal resistive index as measured by Doppler imaging and renal cortical stiffness as assessed by SWE will be explored at each of the 3 time points using the Kruskal–Wallis test.

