## Introduction

Postoperative acute kidney injury (pAKI) is a common complication of aortic aneurysm repair occurring in approximately 40% of patients [1–4]. Even in milder forms, pAKI has been associated with progression to chronic kidney disease (CKD), high mortality, morbidity and health care expense. Although patients may recover renal function after acute injury, there is no curative treatment available [5].

A major impediment to the provision of early and effective treatment for pAKI is the inherent delay in diagnosis due to limitations of available markers of kidney function, which are neither sensitive nor specific to the site, laterality, extent, etiology or reversibility of the injury [6–8]. Additionally, current novel biomarkers of renal injury such as neutrophil gelatinase-associated lipocalin (NGAL) suffer from the limitations of being non-specific to the etiology of renal injury, being heavily affected by preoperative kidney function status [9], lack of current consensus on cut off values [10], and the inability to use as therapeutic targets. As such, the diagnosis of pAKI continues to be delayed with consequential delay in initiation of effective and timely therapy and improved outcomes.

Whereas G1 cell cycle arrest (CCA) biomarkers (urinary insulin growth factor binding protein-7, IGFBP-7 and inhibitor of tissue metalloproteinase-2, TIMP-2) have been recently validated as markers of renal stress that predict the occurrence of pAKI [11, 12], they are affected by preoperative disease comorbidities, do not inform on non-tubular nephron pathology, and have been used in such a way that therapy based on their use has been confined to the postoperative period after the occurrence of the injury [13].

Shear wave elastography (SWE) has evolved as an ultrasound tool capable of measuring and quantifying tissue stiffness in response to stress. Tissue stress is applied by emitted U/S beam that generate shear waves, the velocity of propagation of which is measured as a surrogate of deformation (or elastance or stiffness) using Young’s Elastic Modulus (YM). The stiffer the tissue, the faster the propagation velocity [14]. Shear wave elastography has been recently used to assess renal tissue stiffness in patients with mild forms of chronic kidney disease (CKD) [15–17]. We hypothesize that detection of renal cortical stiffness may add to the diagnostic value of currently used renal biomarkers.

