### Sample size calculation

Based on our prior experience and literature search of a 40% incidence of pAKI in this population encompassing both open and endovascular approaches of descending aortic aneurysm repairs [1, 18, 19], we expect 40% patients to develop pAKI and 60% of patients to not develop pAKI. We project that more than 70% of patients with a positive BSI to develop pAKI, while only 30% of those with a negative BSI to actually develop pAKI. From this assumption, if we recruit 80 patients to the study, we will have 32 patients expected to have pAKI (positive BSI) and 48 patients expected not to have pAKI (negative BSI). Using Fisher’s Exact Test with a 5% two-sided significance level, we will have minimum 90% power to detect the difference between 69% pAKI in patient group who will eventually develop pAKI (positive BSI) and 30% pAKI in patients who will not eventually develop pAKI (negative BSI), when sample sizes are 32 and 48, respectively. In addition, we will recruit 15 healthy group of participants to explore the feasibility of the SWE protocol, and to establish reference values on a sample of our population in terms of renal cortical stiffness, and renal parenchymal and vascular indices.

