### Participants

A total of 80 patients for the ‘study group’ will be enrolled. Each patient will serve as his/her own control by studying the change in BSI from preoperative values to 6 and 24 hr after the procedure. A total of 15 normal healthy volunteers will be enrolled as a ‘feasibility group’ to test the feasibility of the SWE protocol.

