#### Shear wave elastography exam

The ultrasonographic examination of the kidney will be performed using the Mindray Rosana 7 system (Mindray North America, CA, USA) equipped by the SC6-1u transducer for acquiring grayscale, spectral Doppler, and virtual touch tissue quantification on acoustic radiation force impulse (ARFI) imaging in the healthy adults. The exam will be performed by a certified radiology technician with over 10 years of experience and read by an independent radiologist who is blinded to the study protocol. We will use the SWE published and outlined by Sandhu et al. [20] as follows: During each encounter, both kidneys will be evaluated. The flank approach will be used to access both kidneys to minimize dissipation of U/S waves by distances traveled through or by pathology of the spleen and liver for the left and right kidneys, respectively. Exams will be performed in the left and right lateral decubitus positions for imaging the left and right kidney, respectively. Before scanning, we will adjust the image acquisition settings as follows: MI 1.4, image depth 10–12 cm, scanning frequency 3.5 MHz, single focus, dynamic range 65, harmonic imaging, Map E/Space-time 2, and total gain 0–1. The presence or absence of hydronephrosis, calculi, masses, and perinephric collections will be also assessed; the presence of any of these findings and will serve as exclusion criteria. For each participant, the following values will be obtained during suspended respiration: each kidney size in the longitudinal plane; main renal artery peak systolic velocity (PSV), end diastolic velocity (EDV), and resistive index (RI); inferior interlobular artery PSV, EDV, and RI; mid-interlobular artery PSV, EDV, and RI; superior interlobular artery PSV, EDV, and RI; shear-wave velocity values at the renal cortex (five measurements in the longitudinal plane at the upper, upper-mid, mid, mid-lower, and lower poles and three measurements in the transverse plane at upper, mid, and lower poles). All measurements will be repeated to yield two measurements per parameter per observer. Each patient will be scanned by a technician and by the principle investigator (AZ) on the study. Images will be interpreted independently by a radiologist and a vascular surgeon who are blind to the study protocol.

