### Statistical analyses

The analysis plan will include comprehensive graphical and statistical descriptions of the data. Baseline demographics, biomarkers, stratified by pAKI status will be summarized using descriptive summary statistics. Continuous variables will be summarized overall and within each group with the total numbers of observations, means with 95% confidence intervals, standard deviations and ranges. The two-sample t-test will be employed to compare the mean of continuous outcome variables while the Wilcoxon rank-sum test will be used for study outcomes that do not meet the normality assumption after performing appropriate data transformations. Categorical variables will be summarized overall and within each group with the total numbers of observations and percentages with exact 95% confidence intervals. To assess the accuracy and concordance of each marker with the pAKI status, we will calculate sensitivity and specificity. We will evaluate concordance (sensitivity and specificity) between pAKI status and SWE, uCCA, uNGAL alone and in combination. The BSI accuracy in predicting pAKI status will be evaluated in this study. To investigate the prognostic utility of bio-sonographic index for prediction of pAKI status, we will compare the sensitivity and specificity, using the 10% change from baseline to any of the 6 and 24 hour postoperative values alone as well as combined score (range: 0–3). Receiver operating curve (ROC) will be constructed for comparison between individual and combined components of SWE, uCCA, and uNGAL, and the differences in areas under the curve (AUC) will be assessed using a critical “z” ratio proposed by Hanley and McNeil. Intra-subject variability will be examined by comparing difference of individual readings from the median YM for each subject. The diagnostic performance of SWE and combination of each for distinguishing normal renal parenchyma from renal parenchyma affected by AKI will be assessed using a univariate logistic regression model to construct receiver operating characteristic (ROC) curves. ROC analyses will be performed to determine a cut-off point of SWE that would correctly classify the maximum number of participants based on sensitivity and specificity values. Wald asymptotic 95% confidence limits will be presented for sensitivity and specificity values. Percentile method 95% confidence intervals for ROC curves will be generated using the pROC package in R version 3.0.2 (Vienna, Austria) [28, 29]. Comparisons of area under the curves will be performed by use of a contrast matrix to take differences of the area under the empirical ROC curves. Pearson correlation coefficients will be used to assess the strength of association between continuous exposure variables. Stratified analysis of the control and AKI groups will be performed to evaluate for potential significant confounders of SWE values. SAS version 9.4 (Cary, NC) will be used for all other non-ROC related statistical analysis. Two-tailed p values of less than 0.05 will be deemed statistically significant.

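### A group-comparison test (Kruskal-Wallis) is named for the relationship between two continuous measures, resistive index and cortical stiffness, with no groups defined

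*Protocol article*

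**What the plan says.** The subsection of the Protocol article on vascular resistance and cortical stiffness, under Exploratory analyses, sets out to study "The relationship between renal vascular indices in the form of renal resistive index as measured by Doppler imaging and renal cortical stiffness", with the latter taken from SWE. It states that this relationship "will be explored at each of the 3 time points using the Kruskal–Wallis test".

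Both quantities are numeric. The section on the shear wave elastography exam records a resistive index for the main renal artery and three interlobular arteries, and shear-wave velocities at several cortical sites. The Introduction expresses stiffness through Young's modulus. The protocol gives no categories or cut-offs for resistive index. It also names no other grouping factor for this analysis.

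The Statistical analyses section gives a general rule for pairs of continuous measures: "Pearson correlation coefficients will be used to assess the strength of association between continuous exposure variables". It also sets the significance rule: "Two-tailed p values of less than 0.05 will be deemed statistically significant".

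**The concern.** Kruskal-Wallis needs one outcome and a set of independent groups. Here there are two continuous measurements on the same patient at the same time, and the question is how they move together. An analyst following the sentence would have to invent the groups, and could do so after seeing the data.

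Two things are at stake. First, even a sensible grouping yields only a p-value for some difference in stiffness between groups. The reader would not learn how strong the association is or which way it runs, and that is the purpose of studying a relationship. Second, grouping a continuous variable discards information, and this study is small. The Discussion suggests that the Doppler measures may prove useful in the acute setting, so a missed or uninterpretable association would cost the authors something.

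**Working it through.** The protocol states no figure for this analysis, so there is none to reproduce. The check has two parts: whether any grouping factor can be read from the text, and what the test delivers under the one reading that works.

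**Step 1. Candidate grouping factors**

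- *Time point.* Ruled out, because the test is run separately at each time point.
- *Postoperative AKI status.* This would compare one measure between patients with and without AKI. It would not relate the two measures to each other.
- *Each distinct resistive-index value as its own group.* The statistic is H = 12/[N(N+1)] × Σ nⱼ(R̄ⱼ − (N+1)/2)². With every nⱼ = 1 and no ties, the sum of squared rank deviations is N(N²−1)/12, so H = N − 1 whatever the data. For N = 80, H = 79 on 79 degrees of freedom and p = 0.48. This carries no information.
- *Categories of resistive index.* This works, but the protocol defines none.

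**Step 2. What the workable reading gives**

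H is a sum of squares and does not depend on the order of the groups. It therefore has no sign, and it is not an estimate of association.

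**Step 3. Power of the workable reading**

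Inputs from the protocol:
- Study group of 80 (Participants: "A total of 80 patients for the ‘study group’ will be enrolled").
- Expected postoperative AKI in 40%, so 0.40 × 80 = 32 (Sample size calculation).
- Two-sided 5% level (Statistical analyses).

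Assumptions not in the protocol: a bivariate normal distribution, a true correlation of 0.4, and equal-sized resistive-index groups. Rank tests on these groups do not depend on the measurement scales.

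Simulated power (4,000 runs; independent repeats agreed to within about one to two percentage points):

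| n | Kruskal-Wallis, 2 / 3 / 4 groups | Spearman |
|---|---|---|
| 32 | about 40% / 38% / 34% | about 58% |
| 80 | about 80–82% across groupings | about 94% |

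The loss is 58 − 40 = 18 to 58 − 34 = 24 percentage points at n = 32, and 94 − 82 = 12 to 94 − 80 = 14 points at n = 80.

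**Step 4. Other correlations**

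A separate simulation (2,000 runs) used tertiles of resistive index:

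| n | True correlation | Kruskal-Wallis, tertiles | Pearson | Spearman |
|---|---|---|---|---|
| 80 | 0.3 | 53% | 77% | 71% |
| 32 | 0.5 | 59% | 84% | 79% |

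At zero correlation all three tests reject in about 5% of runs. The binned test is therefore valid but less efficient.

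**Step 5. Hand check of the correlation benchmark**

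For Pearson, the Fisher transformation gives power ≈ Φ(atanh(ρ)·√(n−3) − 1.96). With ρ = 0.4, atanh(0.4) = 0.424.
- n = 32: 0.424 × √29 = 2.28, and Φ(0.32) ≈ 63%.
- n = 80: 0.424 × √77 = 3.72, and Φ(1.76) ≈ 96%.

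Spearman should sit slightly below these values under normality, as it does in Step 3.

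**The case against.** The strongest reply is that this is a condensed article, that the analysis is exploratory, and that resistive-index cut-points may sit in a fuller analysis plan. Part of that stands. The absence of cut-points alone would not be a finding, and with pre-defined categories the test is legitimate. But the article describes both measures as continuous and positively names a test suited to a different data structure. Exploratory status relaxes error control; it does not make the test report the strength of a relationship.

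A reader might infer more than the text supports:

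- *That the test cannot address the question at all.* It can, once resistive index is grouped, as the power figures show.
- *That the result would be significant whatever the data.* That would require entering resistive index and stiffness as two samples of one variable, so that the test merely detects their different scales. The protocol does not say this, and any rejection rate for it would rest on scales the protocol does not give.
- *That only 32 patients are involved.* The restriction to postoperative AKI appears in the subsection heading and not in the sentence describing the analysis. The heading may only name the topic, so the milder figures at n = 80 matter equally.
- *That the two sections flatly contradict each other.* The Pearson rule is general and does not forbid a further test. If it covers this pair, strength and direction are already planned. The sections are unreconciled, which is less than a contradiction.
- *That the other exploratory relationships share the error.* Those subsections name no test, and the one that includes serum creatinine asks which marker changes earliest, which a correlation would not answer.

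**Conclusion.** The point holds, and it is minor. The protocol assigns a comparison of independent groups to the relationship between two continuous measures and defines no groups. Its only workable reading requires categories of resistive index, gives no strength or direction, and costs power.

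At an illustrative true correlation of 0.4, the loss is about 18–24 percentage points with 32 patients and 12–14 with 80. These sizes rest on the assumed correlation, bivariate normality and equal-sized groups. The mismatch between test and question rests on none of them. The KDIGO outcome, the BSI accuracy analysis and the sample size calculation are untouched.

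**What to change.** In the subsection on vascular resistance and cortical stiffness, replace the Kruskal-Wallis test with a correlation coefficient and its 95% confidence interval between resistive index and SWE stiffness at each of the three time points. Use Pearson, as the Statistical analyses section already provides, or Spearman if normality fails. The rank-based fallback matches that section's own use of the Wilcoxon test for non-normal outcomes.

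If the authors prefer to keep Kruskal-Wallis, they should state the resistive-index categories in advance and report the correlation beside it.

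The cost is one sentence. Data collection and sample size do not change.

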#### Cortical stiffness-biomarker relationship in pAKI

The relationship between the SWE on one side and urinary CCAs and NGAL (biomarkers) values on the other side will be explored to detect the relationship between renal stiffness and markers of tubular stress and injury at the 3 above-mentioned time points.

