### Procedures

The bio-sonographic index (BSI) will be performed on the study patients at baseline- during their preoperative visit, and at 6 hours and at 24 hours after the procedure. The BSI will be composed of SWE, urinary cell cycle arrest (uCCA) and urinary NGAL (uNGAL). Abnormal BSI will be diagnosed as an increase of at least 10% from baseline to any of the 6 and 24 hour time points. Based on an estimated incidence of pAKI of 40% in this population, a probability of abnormal BSI will be estimated as follows (Table 1).

**Table 1 pone.0241782.t001:** The BSI criteria.

AKI	combination	SWE (YM)	uCCA	uNGAL	Patients	AKI %
Y	Abnormal	≥10% = 1, < 10% = 0	≥10% = 1 < 10% = 0	≥10% = 1 < 10% = 0	40%	90%
N	Normal	SWE <10% = 0	< 10% = 0	< 10% = 0	60%	30%

* Values are in reference to a change from baseline to any of time points 2, and 3.

AKI (Y/N) = YM based on SWE & urine biomarkers

AKI: acute kidney injury; SWE: shear wave elastography; YM; Yong Elastic Module; uCCA: urinary cell cycle arrest; uNGAL, urinary neutrophil gelatinase-associated lipocalin; Y: yes; N: no; BSI: biosonographic index; BSI score is the sum of SWE, Biomarker, and NGAL. It is abnormal if ≥ 1. Total score can range from 0 to 3.

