#### Cortical stiffness-biomarker-biochemical relationship in pAKI

The relationship between SWE, biomarkers and serum creatinine across the above-mentioned 3 time points will be explored to compare which of the parameters is capable of detecting the earliest change in renal pathology.

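### Same-visit associations of renal stiffness with resistive index and urinary biomarkers at 6 h and 24 h may reflect pre-existing kidney disease; statements about acute coupling should rest on change from baseline (minor, exploratory)

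*Protocol article*

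**What the plan says.** The visits are fixed under Procedures: "at baseline- during their preoperative visit, and at 6 hours and at 24 hours after the procedure".

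Three analyses under Exploratory analyses bear on this point:

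- **Resistive index and SWE** (Vascular resistance-cortical stiffness relationship in pAKI): the relationship "will be explored at each of the 3 time points using the Kruskal–Wallis test". That is a separate analysis at each visit.
- **SWE and urinary biomarkers** (Cortical stiffness-biomarker relationship in pAKI): the section speaks of CCA and NGAL values, and the relationship "will be explored to detect the relationship between renal stiffness and markers of tubular stress and injury at the 3 above-mentioned time points". No statistic is named.
- **SWE, biomarkers and creatinine** (Cortical stiffness-biomarker-biochemical relationship in pAKI): the relationship across the three visits is examined "to compare which of the parameters is capable of detecting the earliest change in renal pathology".

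The first two state neither a change from baseline nor a baseline adjustment. Under Participants and Procedures, by contrast, the BSI uses each patient as his or her own control and is defined by a rise of at least 10% from baseline. The Discussion defends that choice.

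On pre-existing disease, the Introduction describes NGAL as "being heavily affected by preoperative kidney function status" and says that CCA markers are affected by comorbidities present before surgery. It adds: "Shear wave elastography has been recently used to assess renal tissue stiffness in patients with mild forms of chronic kidney disease". Under Exclusion criteria, the only limit on kidney function is an eGFR below 15 ml/min/1.73 m².

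**The concern.** A marker value at 6 h or 24 h is the patient's preoperative level plus whatever surgery added. If chronic kidney disease raises both stiffness and a urinary marker, patients with more of it will be high on both at every visit. The two will then correlate after surgery even if their acute changes are unrelated. By the protocol's own account this is plausible for the urinary markers, and the cohort admits chronic disease down to an eGFR of 15.

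The section headings place these analyses in pAKI, and the Discussion hypothesises acute changes that raise cortical stiffness. A reader could therefore take a 24 h association as evidence that acute stiffening goes with tubular stress or injury. The reverse error is also possible: chronic variation can dilute a real acute link or even change its sign. The Discussion plans to use these data to evaluate other biomarkers within the index and to go on to a randomised trial, so the interpretation has some consequence. The AKI outcome, the BSI definition and the sample size are not affected.

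**Working it through.** **The plan's own figure.** The protocol gives no number for these associations. Its one power statement (Fisher's exact test, 69% against 30%, groups of 32 and 48, two-sided 5%, at least 90%) reproduces at 92.8%. This point does not depend on it.

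**Inputs from the protocol.** n = 80 in all. n = 32 (40% of 80) if the analyses are confined to patients expected to develop pAKI. Two-sided 5% level. Pearson correlation, which Statistical analyses names for continuous variables.

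**Assumed inputs.** The protocol gives no variance components, so a range is shown.

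**Check 1: no acute link at all.** A stable disease factor loads with weight λ on each marker's baseline (SD 1). Each marker then receives an independent acute shift with SD 0.5. The expected same-visit correlation is

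r = λ² / (1 + 0.5²) = λ² / 1.25

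so r = 0.09/1.25 = 0.07, 0.25/1.25 = 0.20 and 0.49/1.25 = 0.39 for λ = 0.3, 0.5 and 0.7. Share of 3,000 simulated studies significant at 24 h:

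| λ | r, same visit | Same visit, n = 80 | Same visit, n = 32 | Changes, n = 80 | Changes, n = 32 |
|---|---|---|---|---|---|
| 0 | 0.00 | 5% | 5% | 5% | 4% |
| 0.3 | 0.07 | 10% | 6% | 5% | 6% |
| 0.5 | 0.20 | 43% | 18% | 5% | 5% |
| 0.7 | 0.39 | 96% | 62% | 5% | 6% |

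Results at 6 h agree within simulation error. Correlation after adjusting both markers for both baselines gives 5% to 7%.

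**Check 2: a different parameterisation.** Split each marker's 24 h variance into chronic share c, acute share a and noise e, summing to 1. Let ρc and ρa be the chronic and acute correlations between the markers. Then

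- same visit: r = c·ρc + a·ρa
- change from baseline: r = a·ρa / (a + 2e)

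With c = 0.5, ρc = 0.6 and ρa = 0, the same-visit r is 0.5 × 0.6 = 0.30, significant in about 78% of studies at n = 80 and about 40% at n = 32. At n = 80, ρc from 0.4 to 0.8 gives 43% to 97%. At a weaker c = 0.3 and ρc = 0.4, r = 0.12, significant in about 18% (n = 80) and 10% (n = 32).

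**Check 3: a real acute link, n = 80.**

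- Shares 0.5/0.4/0.1, ρc = 0, ρa = 0.5. Same visit: r = 0.4 × 0.5 = 0.20, power 43%. Change: r = 0.20/0.60 = 0.33, power 86%.
- Shares 0.5/0.3/0.2, same correlations. Same visit: r = 0.15; Fisher z gives atanh(0.15) × √77 = 1.33, power about 26%. Change: r = 0.15/0.70 = 0.21, power about 48%.
- Shares 0.5/0.4/0.1, ρc = 0.6, ρa = −0.4. Same visit: 0.30 − 0.16 = +0.14. Change: −0.16/0.60 = −0.27. The sign differs.

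When ρc = 0, change gives the larger correlation if a + 2e < 1. Since c + a + e = 1, that means e < c. With noise above the chronic share, change scores lose.

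**The case against.** **The sizes come from chosen inputs.** This stands. At a loading of 0.3 the excess over 5% is small, and at n = 32 almost nil. The 86% power for changes is a favourable case; it is 48% with more noise. The checks use Pearson correlation, whereas the protocol names Kruskal–Wallis for resistive index, so for that analysis they show direction only.

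**Same-visit values are partly an inference.** The resistive-index section is nearly explicit. The biomarker section says values and names no method, and an article may leave the scale to a fuller document. This softens the point but does not remove it: what is written describes values at visits and departs from the own-control principle used for the BSI.

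**The documentary support is uneven.** The protocol says that SWE has been used in mild chronic disease, not that it measures it. It says nothing on chronic disease and resistive index, so for that pair the shared cause is an assumption.

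**Safeguards exist.** Urine values are adjusted for albumin and creatinine, and confounders of SWE are to be examined by stratified analysis. Neither adjusts for the patient's own baseline. Including the preoperative visit lets a reader see whether an association was already present, which helps, though no such comparison is stated.

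**Two stronger readings are not supported.** A reader might infer that the third analysis also relies on same-visit relationships and so cannot say which marker changes first. Its text works across the three visits, aims at the earliest change and states no method; that is longitudinal language, and nothing shows a same-visit analysis. A reader might also infer that the study will report a false acute link. The protocol commits to no such conclusion, and describing whether levels agree after surgery is a legitimate aim.

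**Conclusion.** The point holds as a limited one. As written, the SWE–resistive index and SWE–biomarker associations cannot separate pre-existing from acute coupling at 6 h or 24 h, so a postoperative association does not by itself show an acute link. Pre-existing disease is a possible explanation, not a demonstrated one.

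With no acute link, false significance runs from about 10% to 96% at n = 80 and about 6% to 62% at n = 32 over assumed loadings of 0.3 to 0.7, against about 5% on changes. These figures assume a stable disease factor common to both markers, independent acute shifts and Pearson correlation. The analyses are labelled exploratory, so this is a minor improvement in interpretation.

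**What to change.** Keep the same-visit description at all three visits. Add that any statement about acute coupling at 6 h and 24 h will rest on one of two forms:

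- the correlation of changes from baseline, with biomarkers on the log scale, where a change is a ratio and so matches the BSI's percent-change definition; or
- the partial correlation at that visit given both markers' baselines.

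Use the same approach for resistive index and SWE. The third exploratory analysis needs no change on this ground.

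The cost is wording only: the baseline readings are already planned, and no patients or visits are added. The downside is that change scores carry the measurement noise of two readings. The partial-correlation form limits this and is the safer choice if SWE repeatability proves poor.
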